#### Process of selecting sessions to audio record

Ten adherence therapy sessions, chosen at random, will be audio recorded, transcribed and rated using the Adherence Therapy Checklist (fidelity measure) (Gray et al., 2006). The process of randomly selecting sessions for recording will be as follows. Patients will be assigned session number (e.g. patient one will be assigned session one through eight; patient two, nine through 16 etc.). We will use a random number generator to put the 160 sessions into a random order. The researcher will select the first ten sessions. When these sessions occur, the researcher will check consent with the participant and audio record the session. If the patient declines, the researcher will move to the next session on the list until ten sessions have been recorded.

#### Recording of qualitative interviews

Participants in both groups will be interviewed between weeks 12 and 14. The purpose of the interview will be to elicit participants’ feedback about the acceptability of trial procedures and adherence therapy (intervention group only). A smartphone (only used for the trial and disconnected to the internet) will be used for audio recording interviews. Immediately following the interview, the audio file will be uploaded to the University research drive and deleted from the smartphone. Interviews will be transcribed by the researchers (in Arabic) and sent to participants for checking. Any identifiable information will be removed from the transcripts.

#### Analysis

4.12.1

We will report summary statistics (number, percentage) against each of the study aims (e.g., *N* = X patients expressed an interest in participating in the study of which *N* = X (x%) consented to participate).

##### Qualitative data analysis

Transcripts will be translated from Arabic to English before coding and analysis. The translation will be done using two steps of translation: forward and backward by two bilingual persons. FA will translate the original Arabic transcripts into English, and then, another bilingual translator will do the backward translation. The two bilingual persons will then agree on a final English version of each transcript.

Qualitative data will be analysed using inductive approaches within thematic analysis following the six steps described by Braun and Clarke (Braun & Clarke, 2006) with themes and codes driven by the data. The steps start with the researchers becoming familiar with the data by reading the transcripts and generating initial ideas from the data to create codes. Two researchers will read the transcripts independently and code the data. Identified codes will be discussed for coherency, consistency and fit with the research group with modifications made by consensus of the group. Identified codes will be combined to create themes and subthemes. Each theme will then be identified and defined, and a thematic map will be generated.

### Data monitoring

4.13

#### Data safety and monitoring board (DSMB)

Because this is a clinical trial that does not involve a medicinal product, a DSMB is not required.

#### Harms

In our trial, we will adopt the Good Clinical Practice (GCP) definition of adverse events, that is “any untoward medical occurrence in a patient or clinical investigation subject […] which does not necessarily have a causal relationship with this treatment.” The researcher will monitor for any adverse events that have occurred during the study period. Safety reporting will comply with the Australian Clinical Trial Handbook ("Australian Clinical Trial Handbook", 2018).

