#### Primary outcome (feasibility)

4.9.1

The primary outcome of this trial is the feasibility of recruiting people diagnosed with type 2 diabetes to adherence therapy trial in a Middle Eastern context. Our feasibility outcomes are, therefore, the number of patients:

Asked about the study who express an interest in participating and request further information.That need to be asked to get one to provide informed consent.That complete baseline measures.Who complete treatment (defined as attending five of eight sessions with a session being defined as talking on the phone for at least ten minutes).Who complete postintervention measures.

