#### Participant timeline

4.10.1

Initial patient screening and consent to approach will be undertaken by the treating team when the patients attend for routine hospital appointments. The researcher will explain the study and obtain online consent within 2 weeks of consent to be approached being obtained (week one). Baseline measures (week two) will be completed within a week of online consent being obtained. Participants will be randomized and informed of group allocation by FA within 2 days of baseline measures being completed. In the intervention group, patients will receive at least weekly sessions of adherence therapy (week three through 12). The intervention will be delivered by telephone and will be no more than 30 min in duration. Treatment will be finished within 10 weeks of the baseline assessment being completed. Patients will be defined as treatment completers if they attend at least five sessions. A completed session is defined as being of at least ten minutes in duration. Qualitative interviews and follow‐up assessments (study end point) will be completed between weeks 13 and 14. The draft CONSORT flow chart can be accessed via Figshare: https://latrobe.figshare.com/articles/CONSORT_feasibility_randomised_controlled_trial_of_adherence_therapy_in_type_two_diabetes_pdf/9724133

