#### Sample size

4.10.2

This study will not evaluate the efficacy of adherence therapy; consequently, a formal sample size calculation is not required. There is no clear convention about the number of participants required in a feasibility trial. However, a number of authors have stated that at least 30 participants are required to draw reasonable conclusions about the feasibility of conducting a full trial (Arain et al., 2010; Julious, 2005). Therefore, the sample size in our trial will be 40 patients with a 1:1 randomization ratio.

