#### Blinding

4.10.5

This is an open‐label study. Both the participants and the researcher will be aware of group allocation. Because this is a feasibility trial, the risk of bias that this may introduce is not of particular concern.

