#### Governance

4.13.2

All of the investigators have a current Good Clinical Practice certificates. An independently chaired trial steering committee (TSC) reporting to the School Research Committee will have oversight of the conduct of the trial. The committee will meet 4 times during the trial. FA will report recruitment against target and any adverse events that occur during the trial. Patients who suffer from adverse events during our trial will have access to the National Guard Hospital emergency room and can contact MM to schedule appointment for consultation. This has been included in the consent form. The data will be stored on La Trobe University research servers. An anonymized data set will be published with the results manuscript.

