### Limitations

5.2

The researcher is delivering the therapy and collecting outcome data. This may introduce the potential for bias and coercion. Also, participants will not be blinded in this study. Some of the medical information such as HbA1c will be self‐reported. This feasibility study does not have the power to test differences between groups.

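### Adverse events are monitored by the unblinded therapist, who has up to eight planned calls with each therapy patient and no listed contact with controls before follow-up, so ascertainment is likely to differ by arm

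*Protocol article*

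**What the plan says.** All references are to the protocol article.

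- **Who monitors.** Harms: "The researcher will monitor for any adverse events that have occurred during the study period". The section adopts the broad Good Clinical Practice definition, in which an event counts whether or not treatment caused it, and says that safety reporting will follow a national handbook.
- **Who reports.** Under Governance the same researcher "will report recruitment against target and any adverse events that occur during the trial". The recipient is a steering committee that meets four times during the trial.
- **Who that person is.** Limitations: "The researcher is delivering the therapy and collecting outcome data". Blinding: "Both the participants and the researcher will be aware of group allocation".
- **Contact in the therapy arm.** Eight telephone sessions are planned between weeks 3 and 12. Primary outcome defines completion as "attending five of eight sessions with a session being defined as talking on the phone for at least ten minutes".
- **Contact in the control arm.** Usual care only (Treatment as usual). After notification of allocation, the Participant timeline lists nothing from the researcher until the end-of-study assessment and interview. That section places these in weeks 13 to 14; the sections on qualitative interviews give weeks 12 to 14.
- **What is measured.** No adverse event item appears in the primary or secondary outcomes, the list of measures or the additional data collected in the therapy group. The interviews are described as covering views of the trial and its acceptability, plus the therapy itself in the intervention group.

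**The concern.** Because the definition of an adverse event ignores causation, events in control patients are as much in scope as events in therapy patients. The route by which they would reach the record is not the same. A therapy patient talks to the monitor about diabetes medication repeatedly over about ten weeks. A control patient has no listed conversation with the monitor over that period. Serious events may surface in either arm. Minor ones are more likely to be mentioned in a conversation and forgotten without one.

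Two things are at stake. First, the steering committee receives its information from this one source while the trial runs, so what it sees before follow-up may lean towards the therapy arm. Second, a feasibility trial exists to test procedures for a main trial, and a harms procedure that works differently by arm would be carried forward. Limitations acknowledges possible bias from the researcher's dual role in connection with outcome data, but does not mention harms.

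**Working it through.** **1. The plan's own figure.** The only stated number that bears on contact frequency is in the section on selecting sessions to record: "We will use a random number generator to put the 160 sessions into a random order". Sample size gives the other input: "the sample size in our trial will be 40 patients with a 1:1 randomization ratio".

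- Patients per arm = 40 / 2 = 20.
- Planned sessions = 20 × 8 = 160. This reproduces the stated figure.

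**2. Planned researcher contacts between allocation and follow-up.**

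| | Therapy arm | Control arm |
|---|---|---|
| All eight sessions attended | 20 × 8 = 160 | 0 listed |
| Every patient attends only five | 20 × 5 = 100 | 0 listed |

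**3. Does usual care fill the gap?** Background gives six-monthly clinic attendance as an example. Patients are approached at a routine appointment, online consent follows within two weeks, and the study ends by week 14. If the six-monthly interval applies, the next routine visit is due about 26 weeks after the approach, later than the roughly 14 + 2 = 16 weeks a patient spends from approach to study end. Educator meetings need a doctor's referral. Usual care is therefore not a dependable substitute, and it is common to both arms in any case.

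**4. What unequal detection would do (illustration only).** Let p be the true risk of at least one event, the same in both arms, and let d_T and d_C be the probabilities that an affected patient is detected in the therapy and control arms.

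- Expected patients with a detected event = 20 × p × d.
- Apparent risk ratio = d_T / d_C, whatever p is.

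The document gives neither p nor d. With p = 0.3 assumed, 20 × 0.3 = 6 patients per arm truly have an event:

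| d_T | d_C | Detected, therapy | Detected, control | Missed, control | Apparent ratio |
|---|---|---|---|---|---|
| 0.9 | 0.7 | 5.4 | 4.2 | 1.8 | 1.29 |
| 0.9 | 0.5 | 5.4 | 3.0 | 3.0 | 1.80 |
| 0.9 | 0.3 | 5.4 | 1.8 | 4.2 | 3.00 |

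With p from 0.1 to 0.5 and d_C = 0.5, the expected number of affected controls missed runs from 20 × 0.1 × 0.5 = 1.0 to 20 × 0.5 × 0.5 = 5.0. With equal detection the expected ratio is 1.00. These ratios only restate the assumed detection probabilities. They show the direction and the arithmetic, not an estimate for this trial.

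**The case against.** A reader might infer that control-arm events certainly will be missed, that they will be reported by arm, and that adherence therapy will therefore look less safe than usual care. The document does not support that reading, for four reasons.

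- **Mechanism.** Harms does not say that events are elicited during therapy calls, and the therapy is described as dealing with beliefs, ambivalence and practical problems. The elicitation procedure may be in the full protocol, which is not shown, so missing detail is not itself the finding.
- **Shared routes.** Both arms are to be interviewed at the end. Any participant may telephone the researcher for help with the questionnaires. All patients have emergency room access and a clinician to contact. The zero above counts listed researcher contacts, not every way an event could come to light.
- **No stated comparison.** Adverse events are not among the objectives or the listed outcomes. The Analysis section plans counts and percentages against the study aims, and Governance mentions no breakdown by arm. Limitations says that the study lacks power to compare groups.
- **Inherent asymmetry.** Telephone therapy against usual care always brings unequal contact.

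All four points stand as limits on the claim, but they do not remove it. The shared routes before follow-up depend on the patient making contact, and the article describes no path from the hospital or clinician to the researcher's record. The interview is by invitation and is not described as asking about health events. Unequal contact is inherent in the design; placing harms monitoring with the unblinded person who has that unequal contact is a stated choice.

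**Conclusion.** The point holds in a limited form. Monitoring and reporting of adverse events rest with the unblinded therapist, who has up to 160 planned calls in one arm and none listed in the other between allocation and follow-up. Unless the same method and schedule are used in both arms, events, and minor ones above all, are likely to be ascertained unequally, with fewer found in controls.

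The size of the shortfall cannot be derived from the document; the ratios of 1.29 to 3.00 follow entirely from assumed detection probabilities. The conclusion assumes that conversation with the monitor makes an event more likely to be recorded, which is plausible but not stated.

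The importance is moderate: there are 20 patients per arm and no planned safety comparison. It still merits a change, because the committee relies on this source, any later by-arm table would inherit the difference, and the remedy is cheap.

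**What to change.** 1. Add the same short set of adverse event questions (for example hypoglycaemia, emergency visits, admissions, other) to the weeks 13 to 14 REDCap follow-up form in both arms, or ask them at the end-of-study interview in both arms.
2. Report all events to the steering committee, from whatever route, with the source of each marked.
3. Base any summary by arm on the common source only, and give the number of responders per arm. List events volunteered in therapy calls separately.
4. State this in Harms, and extend the Limitations remark on the researcher's dual role to adverse events.

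**Cost.** A few items on an existing form and one or two sentences. No clinical rule changes.

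**Downsides.** Recall runs over about 11 weeks (from about week 3 to week 14). Patients who do not complete follow-up contribute nothing to the common source, and completion of post-intervention measures is itself an uncertain feasibility outcome that could differ by arm. For that reason the responder counts must accompany the table, and events from other sources must still be listed. Because the added questions come only at the end, they do not correct what the committee sees earlier; marking the source at least lets it read those reports properly.

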#### Ethics and protocol amendments

4.13.1

Patients in this study will be recruited from the National Guard Hospital in Riyadh. Ethics approval has been obtained from King Abdullah International Medical Research Centre (KMARC) (reference number: RYD‐19–419812–147869) and La Trobe University Human Research Ethics Committee (Reference number: HEC19221). Any changes to the trial protocol will require a formal amendment to the protocol from all the respective parities the LTU ethics committee and the Saudi ethics committee (King Abdullah International Medical Research Centre (KMARC)).

#### Governance

4.13.2

All of the investigators have a current Good Clinical Practice certificates. An independently chaired trial steering committee (TSC) reporting to the School Research Committee will have oversight of the conduct of the trial. The committee will meet 4 times during the trial. FA will report recruitment against target and any adverse events that occur during the trial. Patients who suffer from adverse events during our trial will have access to the National Guard Hospital emergency room and can contact MM to schedule appointment for consultation. This has been included in the consent form. The data will be stored on La Trobe University research servers. An anonymized data set will be published with the results manuscript.

## DISCUSSION

5

### Potential study implications

5.1

Previous systematic reviews indicate that there is no clear evidence of an ideal therapy or intervention that helps patients with type 2 diabetes improve their medication adherence (Nieuwlaat et al., 2014; Williams et al., 2014). Therefore, a new intervention method and innovation is necessary to improve medication adherence. Adherence therapy is an interesting potential candidate intervention in patients with type 2 diabetes. As far as we can determine there have been no previous trials of telephone‐delivered adherence therapy in patients with type 2 diabetes in a Middle Eastern context. We therefore propose a two‐part study including, first, a cultural adaptation study followed by a feasibility trial to test telephone‐delivered adherence therapy in patients with type 2 diabetes.

### Limitations

5.2

The researcher is delivering the therapy and collecting outcome data. This may introduce the potential for bias and coercion. Also, participants will not be blinded in this study. Some of the medical information such as HbA1c will be self‐reported. This feasibility study does not have the power to test differences between groups.

### Conclusion

5.3

Poor adherence to diabetes treatment is an important public health issue.Adherence therapy is a promising intervention that has not been applied in people with type 2 diabetes in Middle Eastern context.We will undertake a transcultural adaptation of adherence therapy in a Middle Eastern context.This study will establish if adherence therapy delivered via telephone is an acceptable intervention for patients with type 2 diabetes.The feasibility of conducting a full randomized controlled trial to test the effectiveness of adherence therapy in patients with type 2 diabetes will be established in this study.This protocol adheres to the SPIRIT guidelines for clinical trial protocols and was prospectively registered with the Australian and New Zealand Clinical Trials Registry.This study will establish if adherence therapy is an intervention that may be incorporated into the practice of nurses working with people with diabetes.

## TRIAL REGISTRATION

6

The trial protocol was prospectively registered in the Australian New Zealand Clinical Trials Registry (ANZCTR) on the 07/06/2019 trial ID: ACTRN12619000827134.

## Data Availability

As this is a protocol, there are no data to present.
